**Funder** **Orthopaedic Institute Ltd, Oswestry**

## **BACKGROUND**

FSHD sufferers live a long life with disability. Symptoms may develop in early childhood and weakness usually noticeable in the teenage years with 95% of affected individuals manifesting disease by age 20 years. The disorder impacts on the upper extremity and torso, impacting negatively on the muscle mass, shoulder mobility and functional tasks. Consequently chronic disuse of the shoulder negatively impacts independence of sufferers, prospects of employment and staying at work. Secondary features of chronic pain and fatigue also impact quality of life. The disease progression is slow, but highly variable and does not affect life expectancy. Cost of illness analysis per FSHD patient has been estimated to be around £7000 per annum^4. At present there is no known cure and knowledge regarding the mechanisms underpinning FSHD is not sufficient to halt the progression of the disease via pharmacological interventions or gene therapy. Surgical interventions are used to improve scapular stabilisation but long term effect on disease progression is limited.

Several studies have shown that exercise with moderate weights or resistance is not detrimental to sufferers with FSHD. More recently, a study showed that consistent aerobic training in sufferers with FSHD not only improves cardiovascular fitness but also improves strength. Two systematic reviews published in 2013 identified that moderate intensity exercise is generally not harmful in muscular dystrophy sufferers. However detrimental effects are possible, dependent on the protocol and subject. Both systematic reviews concluded that there is insufficient evidence regarding its effectiveness. In addition, these findings mainly apply to lower extremity exercise and only one study focussed specifically on FSHD sufferers. Assisted arm cycling (where the crank is moving itself) has been used successfully in young Duchenne Muscular Dystrophy sufferers. In a case study of a severely affected FSHD patient (including loss of mobility), assisted arm cycling was employed as part of an exercise intervention. The passive nature of this task could potentially explain the lack of improvement in the majority of functional assessments. Thus the feasibility of maintaining arm cycling for exercise purposes at an intensity that will induce muscular adaptations is currently unknown.

We believe that arm cycling has the potential to be effective in maintaining or improving shoulder muscle functioning. However, there is no evidence for its safety or effectiveness in the upper extremity. Our aim is to establish the ability of FSHD sufferers to perform arm cycling (stage 1) to underpin the future design of an arm exercise trial (stage 2). Our hypothesis is that the limited range of shoulder movement and muscle weakness should not impact the ability of FSHD sufferers to perform arm cycling.

## **STUDY OBJECTIVES**

### **PRIMARY OBJECTIVE**

The main objective of this stage of the study is to determine whether FSHD sufferers are physically capable of performing arm cycling.

### **SECONDARY OBJECTIVES**

The secondary objective of this stage of the study is to determine what duration, resistance and cadence (speed) of arm cycling each participant can achieve.

## **TRIAL DESIGN**

This is a pilot study to determine the feasibility of arm cycling as an exercise intervention in FSHD sufferers and to inform the design of a larger trial of an arm cycling exercise intervention.

## **PARTICIPANT SELECTION AND ENROLMENT**

Potential participants will initially be identified from the medical records kept for FSHD patients at the RJA Orthopaedic Hospital, by members of the neuromuscular clinical care team. Medical notes will be reviewed for patients that seem to be eligible for the study, then the invitation letters sent to their home address. They will also be sent a reply slip and a pre-paid envelope, to inform the study team whether they are interested (or not) in taking part in the study.

Once potential participants have indicated that they are interested in taking part in the study, the CI or another suitably qualified member of the research team will determine whether they are eligible via a telephone call, as per the inclusion/exclusion criteria below. Should we need to recruit participants via the FSHD register and/or FSH-MD charity, potential participants will only be approached (by telephone) after they have registered their interest in taking part in the study. Confirmation of molecular genetics result from local neurologist/ GP/ molecular genetics lab will be organised for potential participants prior to the visit.

## **INCLUSION CRITERIA**

Patients will be deemed eligible to take part in the study if they full fill the following inclusion criteria:

1. Aged 18-60 years
2. Genetically confirmed diagnosis of FSHD
3. Willing to attend the assessment session
4. Able to understand the participant information sheet and provide written informed consent

## **EXCLUSION CRITERIA**

Patient will be deemed ineligible for the study if they fulfil any of the following exclusion criteria:

1. Aged <18 years or >60 years
2. Co-morbidity that would affect their ability to perform arm cycling
3. Unwilling to complete the assessments of the study

4. Unable to understand the participant information sheet and provide written informed consent.

## **WRITTEN INFORMED CONSENT**

Written informed consent will be obtained from eligible participants upon their arrival at the Robert Jones and Agnes Hunt Orthopaedic Hospital for the study assessment session. The participant will have the opportunity to discuss the study and ask any questions they may have before consent is obtained by the CI or an appropriately qualified member of the research team. The original consent form will be stored in the trial master file, a copy given to the participant for their records and a copy will be added to their medical notes (where available).

Following consent, the participants will be allocated a trial specific ID number. This ID number will be used on all subsequent trial paperwork relating to the participant.

## **STUDY PROCEDURES**

Participants will be asked to attend **one** assessment visit at the Robert Jones and Agnes Hunt Orthopaedic Hospital NHS Foundation Trust. Participants will undergo an arm cycling exercise session. Prior to exercise patients will have familiarisation on machine followed by 5 minutes rest prior to commencing arm cycling.

### **EXERCISE SESSION**

Participants will perform arm cycling using a table-top arm cyler. Cadence and resistance of the exercise will be determined as per each individual's tolerance. All exercise will be supervised by the neuromuscular specialist physio, to ensure it is completed safely. Participants will be able to have plenty of breaks during the assessments.

The arm cycle will be placed on table with height adjusted to be the same as the acromion (highest point on shoulder). Participants will start arm cycling at a low intensity and increase as per tolerance. They will exercise for a maximum of two minutes at a time, followed by a rest period for 30 seconds. In this manner 5 cycles of exercise and rest would be performed. The exercise sessions are anticipated to last a maximum of 20 minutes, depending on the patient's abilities.

### **OUTCOME MEASURES**

The following measures will be assessed (and recorded in the participant CRF) prior to exercise:

- The Oxford Shoulder Score (OSS) a 12 item shoulder instability questionnaire. The OSS is a validated scoring system used to assess the degree of pain and disability caused by shoulder pathology.
- The range of movements at shoulder and elbow joints will be recorded by goniometer.
- Strength of muscles at shoulder and elbow joint with portable hand held dynamometer. Muscle tested must have ability to move against gravity. "Make test" is performed where

the participant holds isometric contraction for 3-5 seconds. Dynamometer is held perpendicular to the muscle being tested at a set distance from the joint. 2-3 maximum voluntary isometric or eccentric contractions are completed and scores summed.

- Patients would have a familiarisation with arm cycling and commenting about rate of perceived exertion (RPE). This will be followed by 5 minutes rest prior to starting the exercise.

Measurements during exercise:

- Patient selected resistance and cadence (both relate to the intensity of cycling)
- Patient rating of perceived exertion ('effort') during arm cycling using the Borg Rate of Perceived Exertion (RPE) scale for each cycle of exercise.
- 
- Video analysis of shoulder and elbow joint angles during arm cycling. Recording perpendicular to the plane of movement will be done. Primary view should be the sagittal view that will allow measuring wrist, elbow and shoulder flexion and extension.

Clearly visible marker will be placed on the distal head of fifth metacarpal bone, styloid process of ulna, lateral epicondyle of humerus, and lateral aspect of acromion process and most lateral part of hip on the side. That way it can be digitized and joint angles calculated by the lines between these points. The shoulder flexion extension can be relative to the person's position, or relative to the vertical. The marker on hip would help for indication of trunk orientation.

Measurements after exercise:

These are subjective questions and patients comments recorded in their verbatim:

- Patient suggestions about factors that limit their performance.
- Would they consider doing arm cycling if effectiveness is proved?
- Patients will receive a phone call 4 days later to ask "were there any consequences of the arm cycling you did 4 days ago, either positive or negative?"

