## **SAMPLE SIZE**

We plan to recruit 20 FSHD sufferers to take part in this study. This sample size is appropriate for a pilot study, intended to inform the design and sample size of a future larger study of around 60 patients. This would be the size of a study comparing between baseline and post-intervention, assuming the exercise will have an effect size (change in outcome divided by baseline SD) that can be considered "medium", and that a moderate correlation exist between baseline and post-intervention outcome ( $r=0.5$ ). In that case, using a sample

size of 20 patients will minimize the total sample size for the pilot phase and the “real” clinical trial. no sample size calculations have been made here.

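### Strength is scored as an undivided sum of two or three contractions of unspecified type, so participants of equal force can score up to 50% apart

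*Protocol*

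**What the plan says.** The strength bullet in the protocol's Outcome Measures section, among the measures taken before exercise, contains two statements that matter here.

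- **The test.** It is a make test with a portable dynamometer in which "the participant holds isometric contraction for 3-5 seconds".
- **The score.** "2-3 maximum voluntary isometric or eccentric contractions are completed and scores summed".

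The protocol does not say when two contractions are done and when three, or when a contraction is isometric and when eccentric. The score is a plain sum, not divided by the number of contractions. The section introduces these measures with "The following measures will be assessed (and recorded in the participant CRF) prior to exercise", but does not say whether the CRF holds the individual readings, the number completed or only the total.

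Strength is measured once, at a single visit (Study Procedures). The primary objective is to "determine whether FSHD sufferers are physically capable of performing arm cycling". The secondary objective concerns the duration, resistance and cadence achieved. The Background gives the hypothesis that limited shoulder movement and muscle weakness should not affect the ability to cycle.

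**The concern.** A sum over a number of repeats that may differ between people measures two things at once: how strong the participant is and how many contractions were done. Two participants with the same force get different scores if one does two and the other three. Mixing contraction types adds a second source of difference that is not strength, and it contradicts the isometric test described in the same bullet.

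Three uses of the score are exposed:

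- the description of how weak the participants are;
- any examination of whether weakness relates to cycling ability. Error unrelated to strength pulls such a relation towards zero, and the hypothesis is that weakness has no effect, so the error would tend to favour it;
- any strength SD taken from this pilot to plan stage 2. The Sample Size section says the pilot is to inform the later study's design and size, and it defines effect size as change divided by baseline SD.

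**Working it through.** The protocol gives no figure for the strength score, so there is nothing to reproduce. The check is arithmetic on the scoring rule.

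**Inputs from the protocol.** The count k is 2 or 3. The score is a sum. The type is isometric or eccentric.

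**Assumptions (not in the protocol).** Force per contraction, F, is the same at each repeat for a given participant. For the effect on spread, half the participants do two and half do three, independently of F. The true between-participant CV of F is taken as 20%, 30% or 50%. For the effect of type, the ratio of eccentric to isometric force is taken as 1.0 to 1.3.

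**1. Count alone.** Score S = k × F. Two contractions give 2F and three give 3F, a ratio of 3/2 = 1.50. With F = 50, the scores are 100 and 150. A mean or maximum gives 50 in both cases.

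**2. Count and type together.** Three eccentric against two isometric contractions give a ratio of 3 × (eccentric/isometric) / 2. Over force ratios of 1.0, 1.1, 1.2 and 1.3 this is 1.50, 1.65, 1.80 and 1.95. Only the 1.50 follows from the protocol; the rest depends on the assumed force ratio.

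**3. Spread, with count independent of force.** The mean of k is 2.5 and its variance 0.25, so CV_k² = 0.25 / 2.5² = 0.04. For a product of independent quantities, CV_S² = CV² + 0.04 + 0.04 × CV². The correlation of S with F is CV / CV_S.

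| True CV | CV_S² | CV_S | Relative variance, CV_S²/CV² | Correlation with true strength |
|---|---|---|---|---|
| 0.20 | 0.0400 + 0.04 + 0.0016 = 0.0816 | 0.286 | 2.04 | 0.70 |
| 0.30 | 0.0900 + 0.04 + 0.0036 = 0.1336 | 0.366 | 1.48 | 0.82 |
| 0.50 | 0.2500 + 0.04 + 0.0100 = 0.3000 | 0.548 | 1.20 | 0.91 |

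If the count is also unrelated to the cycling measure, an observed correlation between strength and cycling is the true one multiplied by the last column. At a CV of 30% it is 0.82 times its true size.

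**4. Spread, with count following strength.** Take the extreme case: everyone below median force does two and everyone above does three. Let F be normal with mean 1 and SD 0.30, so the mean absolute deviation is 0.30 × √(2/π) = 0.239.

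- Mean of S = 2.5 + 0.5 × 0.239 = 2.620.
- Mean of S² = 6.5 × 1.09 + 2.5 × 2 × 0.239 = 8.282.
- Variance = 8.282 − 2.620² = 1.419, SD = 1.191, CV_S = 1.191 / 2.620 = 0.455.
- Covariance with F = 2.5 × 0.09 + 0.5 × 0.239 = 0.345, so the correlation = 0.345 / (1.191 × 0.30) = 0.96.

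A lognormal F gives a CV of 0.46 and a correlation of 0.97. In this case the rank order of participants is kept and the correlation barely falls, but the spread grows more than under random counts.

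**The case against.** The strongest reply is that little depends on this score. Capability for arm cycling is the primary objective, and duration, resistance and cadence are the secondary one. Eligibility does not depend on strength, no analysis of it is stated, and with one visit there is no change score to corrupt. This stands, and it limits the severity: the feasibility result is the same however strength is scored.

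Four stronger readings are tempting, and the documents do not support them.

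- **That the SD used to size stage 2 is wrong.** The Sample Size section reaches around 60 patients from an assumed medium effect and a correlation of 0.5, names no outcome, and says no calculation was made. A strength SD might be used later; that is a possibility only.
- **That weaker participants will do fewer contractions.** The protocol links the count neither to fatigue nor to strength, and the Exercise Session section allows ample breaks during the assessments. Such a pattern would also have a different effect: the correlation of 0.82 belongs to random counts, not to counts that follow strength (step 4 of the working).
- **That participants cannot be compared at all.** If the physiotherapist uses one count and one type throughout, the scores are comparable. The fault is that the protocol does not ensure this.
- **That the sum itself must go.** A sum over one fixed count would serve as well as a mean.

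Nor does a statistical analysis plan not shown here answer the point. The protocol itself fixes the test and the score, and a later plan could repair the score only if the individual readings, or at least the counts, were kept.

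**Conclusion.** The scoring rule is wrong as written, with moderate to minor severity. Where the count differs between participants, the score differs by up to 50% at equal force; this is certain arithmetic. The mention of eccentric contractions contradicts the isometric make test in the same bullet, and no other section resolves it.

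The effect on the spread is an illustration. Under a random half-and-half split, a true CV of 30% is observed as about 37%, relative variance rises by 48%, and the correlation with true strength is about 0.82, with 0.70 and 0.91 at true CVs of 20% and 50%. The split and the CVs are assumptions. The feasibility conclusion stands. What would be distorted is the strength description, any relation of weakness to cycling ability, and a strength SD if one is used for stage 2.

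**What to change.** Amend the strength bullet and the CRF as follows.

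1. Reconcile the contraction type with the make test, so that one type is used for every participant and every muscle tested.
2. Score each muscle as the mean or the maximum of its contractions. If the sum is kept, fix one count for everyone. A maximum still depends slightly on the number of attempts when readings vary, so a fixed count is preferable with either score.
3. Record each reading and the number of contractions completed.

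The cost is about a sentence in the protocol and a few CRF fields, with no added visit.

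For data already collected, dividing the sum by the count puts scores on one scale, but only if the count was recorded. It does not repair a mixture of isometric and eccentric contractions. If the type was not recorded, the report should say so and limit the use of the strength data to description.

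### The day-4 call asks only about consequences of arm cycling, although the same visit includes maximal strength tests of the same joints, so delayed effects may be misattributed or missed

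*Protocol*

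**What the plan says.** The protocol's Study Procedures section sets a single attendance: "Participants will be asked to attend one assessment visit". The same section adds "Participants will undergo an arm cycling exercise session".

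The Outcome Measures section lists what comes before cycling under the line "The following measures will be assessed (and recorded in the participant CRF) prior to exercise". One item is "Strength of muscles at shoulder and elbow joint with portable hand held dynamometer", with the instruction that "2-3 maximum voluntary isometric or eccentric contractions are completed and scores summed".

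The Exercise Session section describes cycling as graded: "Participants will start arm cycling at a low intensity and increase as per tolerance". Bouts last at most two minutes and there are five of them.

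After exercise, participants are asked what limited their performance and whether they would take up arm cycling if it proved effective. Four days later they are telephoned with one scripted question: "were there any consequences of the arm cycling you did 4 days ago, either positive or negative". Answers are taken down in the participant's own words.

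The Background section says of arm cycling: "However, there is no evidence for its safety or effectiveness in the upper extremity".

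**The concern.** A participant has to settle the cause of a symptom before deciding whether the question covers it, and is offered only one cause. Someone with a sore shoulder on day 4 may put it down to cycling because cycling is what the caller mentioned, even if the strength tests produced it. Someone who feels more tired, or better, but does not connect this with cycling has not been asked about it.

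What is at stake is the tolerability information passed from stage 1 to stage 2. The Background states that safety in the arm is unknown, and the Trial Design section says the pilot is to inform a larger trial. With 20 participants planned, a few misplaced or missing reports could change how well tolerated the exercise appears. An analysis plan cannot repair this, because the wording of the call decides what is elicited.

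**Working it through.** The protocol gives no figure for delayed effects, so there is none to reproduce. The check sets the sections side by side.

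1. **Same visit.** Study Procedures specifies one visit. Outcome Measures places strength testing before cycling at that visit. At the day-4 call both exposures are therefore equally distant.

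2. **Same joints.** Strength is tested at the shoulder and elbow. Cycling moves the same joints, and Outcome Measures plans video analysis of shoulder and elbow angles during it. The site of a symptom will therefore do little to show which exposure caused it.

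3. **Different intensity.**
   - Testing uses 2 to 3 maximal contractions. With the 3 to 5 second hold given for the make test, this is 2 × 3 = 6 to 3 × 5 = 15 seconds of maximal effort per muscle if the contractions are isometric. The protocol gives no duration for eccentric contractions.
   - Cycling is at most 5 × 2 = 10 minutes, self-selected and starting low, plus a familiarisation of unstated length.
   - Testing is short but maximal; cycling is longer but limited by tolerance. Nothing in the protocol shows which is the likelier source of after-effects. It is enough that testing cannot be ruled out.

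4. **Testing exposure varies between participants.** Only muscles able to move against gravity are tested, so weaker participants may have fewer muscles tested. The chance of misattribution may therefore differ with disease severity.

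5. **Scope of the question.** It asks about cycling only. It mentions neither the strength tests nor any change since the visit regardless of cause.

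6. **Other sources.** No other collection of delayed effects or adverse events appears in the protocol text available.

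7. **Direction of error.** Crediting testing effects to cycling raises the count of apparent cycling effects. Leaving out changes the participant does not link to cycling lowers the count of effects after the visit. Estimating the net error would need the rate of after-effects from each exposure and the probability of each kind of attribution. The protocol gives none of these, so no numerical estimate is offered.

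**The case against.** The strongest reply is that the question is open, invites good and bad effects, and is answered in free words, so a participant can say that the strength test caused the soreness. This stands to the extent that misattribution and under-reporting are risks and not certainties. It does not remove the framing, which still offers one cause.

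Second, neither objective names after-effects: the primary is physical capability, the secondary is duration, resistance and cadence. This stands in full.

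Third, what participants perceive as consequences of cycling is legitimate acceptability information, and the protocol does not say the answers will be reported as a causal rate. This also stands. It is a reason to keep an attribution question, placed second.

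Fourth, the make test is described as isometric, so the eccentric element may not apply. The Outcome Measures text describes an isometric hold and then allows either type; those statements need to be reconciled. The concern survives either way, because the contractions are maximal in both cases.

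Fifth, no wording can separate the two exposures in one group seen once. That is correct, and it limits what the fix can claim.

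A reader might go further and infer that testing soreness will inflate the cycling effect by a calculable amount, or that the answer will bias a stage 2 go/no-go decision. The protocol supports neither: it gives no symptom rates and no number of muscles tested, and it states no decision rule that uses this call. Nor can one infer that delayed safety is recorded nowhere else, since a separate reporting procedure may exist outside the text available.

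**Conclusion.** The point holds as a minor flaw in a fixed question. The day-4 wording ties reporting to one of two arm exposures at the same visit, so after-effects of testing may be credited to cycling and changes not linked to cycling may be missed. Net direction and size are unknown. The capability objective and the secondary measures taken during cycling are untouched; only the tolerability information for stage 2 is affected.

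The conclusion rests on two assumptions: that strength testing takes place at the single visit, as the sections read together indicate, and that the call is the only source of delayed effects, which is true of the protocol text available. If a separate safety procedure exists, fewer events would be lost, but the wording of this outcome would remain one-sided.

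**What to change.** Replace the single question with a short sequence:

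1. Ask neutrally first: *Since your visit 4 days ago, have you noticed any change, for better or worse, in your arms, shoulders or general condition (for example pain or fatigue)?* The prompt should not be confined to the arms, because the Background names fatigue and chronic pain as features that affect quality of life.
2. For each change, record site and onset.
3. Then ask what the participant attributes it to: cycling, the strength tests, or something else.

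Report the answers as effects following the visit, meaning strength testing plus cycling, and show perceived attribution separately. State that a single-group, single-visit design cannot separate the two exposures.

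The cost is one reworded question, a few extra fields on the record form, and a conclusion slightly less specific to cycling. Neither the testing nor the exercise changes.
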